#### 134        INTERVENTIONS

##### 135        Control Group (CG):

136        They will receive standard treatment, which includes protocols for delirium or functional decline  
 137        prevention, with removal of physical and pharmacological barriers and daily mobilization.

##### 138        Intervention Group (IG):

They will receive physical training (PT) and health education. The PT program will consist of muscle strengthening exercises, balance training, gait stimulation, and inspiratory muscle training. The duration and intensity will be adjusted to the clinical situation and patient availability. Ideally, two PT sessions will be conducted daily (one in the morning and one in the afternoon), with an average duration of 30 minutes each, from Monday to Friday.

Warm-up: Each session will begin and end with a low-intensity warm-up and cool-down period of approximately 3 minutes, during which joint mobility exercises and stretching of major muscle groups will be performed.

Muscle Strengthening ("squats"): The muscle strengthening exercises will consist of a circuit primarily targeting the lower limbs (1-3 sets of 3-10 repetitions), alternating with exercises for the upper limbs (1-2 sets of 3-10 repetitions). They will be performed in a seated position on a chair with armrests, initially with both feet fully supported on the floor (knees flexed at 90°) and the back straight against the backrest (hip flexed at 90°). Starting from the initial position, participants will have to stand up from the chair and sit back down.

Difficulty Levels (not progressing to the next difficulty level until the patient completes 3 sets of 10 repetitions at the starting difficulty level):

1. With assistance, with arm support, without additional load, and with both feet supported.
2. With assistance, without arm support, without additional load, and with both feet supported.
3. Without assistance, without arm support, without additional load, and with both feet supported.
4. Without assistance, without arm support, with additional load, and with both feet supported (progress to the next difficulty level when reaching the maximum load allowed by weighted vests).
5. Without assistance, without arm support, without additional load, and with single-foot support.
6. Without assistance, without arm support, with additional load, and with single-foot support.

Balance: In a standing position, the patient will have to lift one knee for a certain period of time, progressing from 3 to 5 seconds. Subsequently, they will maintain balance by performing the same exercise with their eyes closed, following the same time progression. Up to 3 repetitions will be performed with each leg alternately. To stabilize the patient and provide safety, they will be held by the hands, while providing only necessary assistance.

Gait Stimulation: Patients who can walk with or without assistance will perform a gait stimulation exercise, which consists of walking as much as possible, with or without aid, for 10 minutes. The exercise will always be supervised, with the participant accompanied throughout the course. Participants should be able to maintain a conversation without difficulty breathing while walking. The time (up to a maximum of 10 minutes) and distance covered (according to marks placed in the hallway) will be recorded. When they are able to walk continuously for 10 minutes, the speed of movement will be increased.

Cool-down: Stretching exercises for major muscle groups will be performed, always adapted to individual characteristics of the participants.

Inspiratory Exercises: Participants will perform 30 inspirations through a device provided by the team (Power Breathe® Classic Medium Resistance) against 40% of maximum inspiratory pressure (PImax). Every 5 sessions, participants' PImax will be reassessed to adjust the workload.

Health Education: In each activity session, patients and caregivers will be taught how to perform the exercises to ensure they continue doing them at home, and prior to discharge, an entire session will be dedicated to reviewing the complete program. Essentially, the type, frequency, and progression of exercises to be performed will be reviewed. Participants will be explained how to perform them at home, and personalized written instructions with illustrations of the exercises will be provided. Additionally, one

month and two months after discharge, the professional who conducted the training will make a phone call to emphasize program adherence or address any doubts.

## DATA SOURCE

Data will be obtained through interviews and review of medical records. Upon admission, each patient, family member or caregiver, and the responsible nurse will be interviewed. The patient and nurse will also be interviewed at hospital discharge, and a telephone contact will be made with the patient and family member or caregiver at 3 months post-discharge.

## MEASUREMENT OF VARIABLES

### Primary Variable:

The proportion of patients who, at 3 months post-hospital discharge, recover the Katz index they had two weeks before admission (baseline) will be measured. The Katz index (Katz S. JAMA 1963; 185:914-919) measures the number of Activities of Daily Living (ADLs) performed independently, including bathing, dressing, toileting, transferring from bed to chair, continence, and feeding. For each ADL, a score of 1 is given if performed independently and 0 if any assistance from another person is required. The range is from 0 to 6.

### Measurement of Secondary Variables:

The Barthel Index assesses 10 items (feeding, bathing, dressing, grooming, bowel control, bladder control, toileting, transferring from bed to chair, ambulation, and stair climbing), with a range from 0 to 100 in 5-point intervals. A lower score indicates greater dependency (Mahoney F. Md Med J 1965; 14:61-65). The Functional Ambulation Classification (FAC) scale (Holden MK. Phys Ther 1984; 64:35-40) assesses walking ability in 6 levels: 0 unable to walk; 1 walks with substantial assistance from one person; 2 requires slight physical contact from one person; 3 walks independently but needs supervision from one person; 4 walks independently on level ground but cannot negotiate stairs; and 5 walks independently on level ground and stairs. These three scales (Katz, Barthel, and FAC) will be measured at 4 time points: 2 weeks before admission (baseline), at admission, at discharge, and at 3 months. The Short Physical Performance Battery (SPPB) (Guralnik JM. J Gerontol 1994; 49:M85-94) assesses the ability to perform three tasks (balance, gait speed, and chair stands) with a total score ranging from 0 to 12. Balance is evaluated by having the participant stand for ten seconds in three different positions: feet together, semi-tandem, and tandem. One point is awarded for each successfully performed position, with a range from 0 to 4. Gait speed is assessed by timing the participant walking 4 meters with or without the use of a cane or walker. Scores range from 4 (less than 4.8 seconds) to 0 (unable to perform). Chair stands measure the time it takes to stand up from a chair five times as quickly as possible without using the arms. Scores range from 4 (less than 11.2 seconds) to 0 (more than 60 seconds or unable to perform). These measures will be taken at admission and discharge. All outcome variables will be assessed by the same properly trained investigator who is not involved in the intervention. An investigator who did not participate in the training will conduct a telephone follow-up at three months post-discharge with the participant or caregiver (from both groups) to assess the functional status of ADLs (Katz index, Barthel index) and ambulation (FAC).

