#### 104        Secondary Objectives:

105        To evaluate the effect of the intervention on recovery at discharge and at 3 months post-hospitalization, in  
 106        terms of functional status measured by other scales of physical function (Barthel Index) and ambulation  
 107        (Functional Ambulation Classification, FAC).

108        To evaluate the effect of the intervention on the change from admission to discharge in functional status  
 109        measured by the Short Physical Performance Battery (SPPB).

110        To evaluate the consistency of differences between the intervention and usual care in subgroups defined  
 111        by age, frailty, presence of delirium, and baseline functional status.

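### The SPPB balance rule (one point for each of three positions) cannot give the stated 0–4 balance range or the 0–12 total

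*Protocol*

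**What the plan says.** The Protocol, under Measurement of Secondary Variables, introduces the SPPB as a battery that "assesses the ability to perform three tasks (balance, gait speed, and chair stands) with a total score ranging from 0 to 12". It then describes each task.

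- **Balance, the test:** "Balance is evaluated by having the participant stand for ten seconds in three different positions: feet together, semi-tandem, and tandem".
- **Balance, the score:** "One point is awarded for each successfully performed position, with a range from 0 to 4".
- **Gait speed:** the top score is 4, for a walk of less than 4.8 seconds, and the bottom score is 0.
- **Chair stands:** the top score is 4, for less than 11.2 seconds, and the bottom score is 0.

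The section cites a published source for the instrument and has it measured at admission and at discharge. Under Secondary Objectives, the change in SPPB between those two times is a named objective. The Protocol mentions no fourth balance position, no position worth two points and no partial credit for a shorter hold.

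**The concern.** The balance scoring sentence contradicts itself: its rule and its range cannot both be right. The range feeds the total, so the rule also contradicts the stated maximum of 12.

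This is a rule that the Protocol states, and states inconsistently, so it is not a detail left for an analysis plan. The passage is continuous prose with no table or redaction that could explain the mismatch.

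The quantity at stake is a named secondary outcome, and balance is one of the components that the intervention trains. If the rule were applied as written, patients could not be credited with the top balance score. The recorded total would then run on a shorter scale than the one the Protocol names.

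**Working it through.** **Inputs**, all from Measurement of Secondary Variables:

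- balance positions: 3
- points per position: 1
- stated balance range: 0–4
- gait speed maximum: 4
- chair stands maximum: 4
- stated total range: 0–12

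**Step 1. The stated total from the stated component ranges.** Maximum total = balance + gait + chair = 4 + 4 + 4 = 12. This reproduces the stated figure, so the two ranges are consistent with each other.

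**Step 2. The balance range from the stated rule.** Balance score = number of positions passed × 1 point. Passing 0, 1, 2 or 3 positions gives 0, 1, 2 or 3. The maximum is 3 × 1 = 3. The stated 4 is not reproduced.

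**Step 3. The total from the stated rule.** Maximum total = 3 + 4 + 4 = 11. The stated 12 is not reproduced.

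| | Stated range | Rule as written |
|---|---|---|
| Balance maximum | 4 | 3 |
| Gait speed maximum | 4 | 4 |
| Chair stands maximum | 4 | 4 |
| Total maximum | 12 | 11 |

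**Step 4. Size of the gap.** One balance point of four: 1/4 = 25% of the balance scale. One total point of twelve: 1/12 = 8.3% of the total scale. The largest recordable improvement from admission to discharge falls by the same single point, from 4 to 3 on balance and from 12 to 11 on the total.

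**Step 5. Which part is wrong?** Two statements (0–4 and 0–12) support each other, and one (a point per position) conflicts with both. The simplest reading is that the sentence describes the balance rule incompletely and that the ranges are as intended. The Protocol does not say how the fourth point is earned, so the text alone cannot settle the rule.

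**The case against.** The strongest reply is that this section is a summary and not a scoring manual. For gait speed and chair stands it gives only the end anchors and no cut-points for scores 1 to 3. Nobody could score the battery from this paragraph, so the assessor must be using the cited instrument or its form, and the intended scale is not in doubt. Much of this stands. It makes literal scoring less likely, and it is why the consequence has to be stated conditionally. It does not remove the contradiction, because for balance the Protocol gives what reads as a complete rule, and that rule gives the wrong range.

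A reader might also infer more than the documents support:

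- **Disagreement between assessors adds noise.** The same section assigns all outcome assessments to one trained investigator outside the intervention. The Design section speaks of evaluators in the plural, which leaves a small gap, but nothing suggests mixed scoring.
- **One point is large next to the change expected in hospital.** The Protocol gives no expected SPPB change, standard deviation or important difference, so no such comparison can be made.
- **The trial's comparison is biased.** A shared ceiling applies to both groups. It could blunt a real difference among the best balancers, but it does not favour either group directly.
- **Past tests can simply be re-scored from hold times.** The Protocol describes a ten-second stand and a point for success. It does not say that hold times are recorded.

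**Conclusion.** The point holds, as a minor one. The per-position rule contradicts both stated ranges. The arithmetic is exact: balance reaches 3 where 4 is stated, and the total reaches 11 where 12 is stated.

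Any effect on data assumes that balance was, or will be, scored literally. In that case the top point is lost in both groups and the total is not comparable with a 0–12 scale. The Protocol does not allow an estimate of how many patients would reach that point. The preceding trial that it summarises had a mean age of 88 years and 70% meeting frailty criteria, but it reports no balance scores.

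The primary outcome is recovery of the baseline Katz index at 3 months, and the sample size rests on that outcome alone. Neither depends on the SPPB.

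**What to change.** Replace the balance scoring sentence with the balance rule from the cited instrument, stating how each point from 0 to 4 is earned, so that balance runs 0–4 and the total 0–12. Confirm that the case report form uses the same rule.

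If any balance tests were already scored to a maximum of 3, correct them where the recorded data allow. Where they do not, report the scale actually used (balance 0–3, total 0–11) and do not present it as 0–12.

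The cost is one corrected sentence and a check of the form. Design, sample size and primary analysis stay as they are.

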### Other Variables:

They will be collected through a standardized questionnaire administered by trained personnel, including: Demographic data. Medical variables: cause of hospitalization and severity (Apache II scale (Crit Care Med 1985; 13:818)), comorbidity (Charlson index (Charlson ME. J Chronic Dis 1987; 40:373-383)), medication use (statins, psychotropics, cholinesterase inhibitors, corticosteroids, diuretics, and cardiovascular medications), history of falls, presence of geriatric syndromes (malnutrition, dementia, pressure ulcers, depression, delirium) diagnosed based on clinical criteria and commonly used scales, and presence of frailty, using Fried's criteria (Fried L, J Gerontol Med Sci 2001; 56A:M146-M156). Body

mass index (BMI), calculated as weight in kilograms divided by height in meters squared. Metabolites in urine.

## SAMPLE SIZE

Calculated by estimating the proportion of patients who recover their baseline Katz index at 3 months post-hospital discharge. In our AGE CAR study, in the control group, 40% of patients recovered their baseline Katz index at 3 months. With the current intervention, we expect that 60% will recover the Katz index at 3 months. Therefore, with a statistical power ( $1-\beta$ ) of 80% and a significance level ( $\alpha$ ) of 0.05 (two-tailed), we need to analyze a total of 188 patients, rounded to the nearest "10," which is 190 patients. Hospital mortality in our unit is approximately 12%, and assuming a 20% loss to follow-up, we will need to include 252 patients, 126 in the intervention group and 126 in the control group.

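### The 252 patients to be included do not leave the 188 to 190 needed for analysis once the protocol's own 12% mortality and 20% loss are applied

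*Protocol*

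**What the plan says.** All the figures stand in the Sample Size section of the protocol.

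- Control arm, taken from the group's previous trial: "in the control group, 40% of patients recovered their baseline Katz index at 3 months".
- Intervention arm: "we expect that 60% will recover the Katz index at 3 months".
- Power 80%, two-sided significance level 0.05.
- Result: "we need to analyze a total of 188 patients", which the protocol then rounds to 190.
- Allowance for losses: "Hospital mortality in our unit is approximately 12%, and assuming a 20% loss to follow-up, we will need to include 252 patients", split equally as 126 per arm.

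The formula that leads from 190 to 252 is not printed. The section does not say whether the 20% applies to all included patients or only to those discharged alive.

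**The concern.** To end with a given number of analysable patients, the target has to be divided by the proportion expected to remain. Multiplying it by one plus the loss rate always gives too small a number, and the gap widens as the losses grow. With combined losses of roughly 30%, the difference is no longer a rounding matter, and 252 looks like the product of multiplication.

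The inclusion target and the 80% power are figures that an ethics committee, a funder and later readers will take at face value. If the losses occur as assumed, a trial that recruits exactly to plan will still fall below its stated power.

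**Working it through.** **Inputs** (all from Protocol, Sample Size): p1 = 0.40, p2 = 0.60, two-sided α = 0.05 (z = 1.96), power 80% (z = 0.8416), mortality 12%, loss to follow-up 20%, inclusion 252 (126 + 126).

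**1. The analysable number is reproduced.** With the unpooled variance, n per arm = (1.96 + 0.8416)² × (0.40 × 0.60 + 0.60 × 0.40) / 0.20² = 94.19, so about 188 in total. The pooled-variance version gives 97 per arm (194 in total), so the plan evidently used the unpooled form. This step is sound.

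**2. The figure of 252 is reproduced only by multiplying up.**

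| Route | Result |
|---|---|
| 95 × (1 + 0.12 + 0.20) | 125.4 per arm, rounded up to 126, total 252 |
| 188 × 1.12 × 1.20 | 252.7 |
| 188 / (0.88 × 0.80) | 267.0 |
| 190 / (0.88 × 0.80) | 269.9 |
| 188 / (1 − 0.32) | 276.5 |
| 190 / (1 − 0.32) | 279.4 |
| 190 / 0.80 (the 20% already includes deaths) | 237.5 |

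The first route gives 252 exactly. No division route does.

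**3. Forward check, which does not depend on how 252 was obtained.**

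- Sequential losses: 252 × 0.88 × 0.80 = 177.4.
- Additive losses: 252 × 0.68 = 171.4.

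The shortfall is 11 to 17 patients against 188, or 13 to 19 against 190. For 252 to leave 188 to 190, total attrition would have to be 1 − 188/252 = 25.4% to 1 − 190/252 = 24.6%. The plan's own rates give 29.6% (sequential, 1 − 0.704) or 32% (additive).

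**4. Power for 60% versus 40% at the numbers that remain.**

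| Analysed in total | Unpooled (the formula that gives 188) | Pooled |
|---|---|---|
| 190 | 80.3% | 79.2% |
| 188 | 79.9% | 78.8% |
| 177.4 (sequential) | 77.6% | 76.4% |
| 171.4 (additive) | 76.2% | 74.9% |

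Within either column, the attrition error costs about 3 to 4 percentage points relative to 190. By the unpooled formula, 80% power at 177 or 171 analysed requires an intervention rate of about 60.6% or 60.9% against 40%.

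**The case against.** The arithmetic itself is hard to dispute. The case on the other side concerns how much it matters and how firmly it can be put.

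- *The effect is small.* This stands. Power falls by 3 to 4 points and the detectable difference grows by less than one percentage point. Neither the type I error nor the estimate is affected.
- *Part of the gap to 80% in the pooled figures comes from the choice of formula.* This also stands: by that formula even 188 to 190 analysed gives only 78.8% to 79.2%. The like-for-like comparison is the unpooled one, 76.2% to 77.6% against 80%.
- *Sequential losses are the more natural reading*, since in-hospital death comes before loss after discharge. That is fair, and it favours 177 analysable and 268 to 270 included. It narrows the shortfall but does not remove it.
- *The multiplication is inferred.* It is, because no formula is printed. The forward check does not need it.
- *The 12% is a unit-wide rate, and the eligibility criteria exclude terminal illness and very short stays.* Mortality among those included might therefore be lower. With 20% sequential loss, 252 would leave 188 only if mortality were about 6.7% (1 − 188 / (252 × 0.80)). The protocol gives no such figure and plans with 12%.
- *Under intention-to-treat, deaths could count as non-recovery.* No mortality allowance would then be needed, and 252 × 0.80 = 202 would suffice. But the Statistical Analysis section gives deaths no outcome, and the Sample Size section treats mortality as a loss from the analysed number.

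None of these readings makes 252 agree with the stated inputs.

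**Conclusion.** The point holds: the inclusion total is wrong as written. Under the protocol's own loss rates, 252 patients yield about 177 (sequential) or 171 (additive) for analysis instead of 188 to 190. Power is then 77.6% or 76.2% by the formula that produced 188, and 76.4% or 74.9% with pooled variance. An inclusion total consistent with the stated target lies between 268 and 280.

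This rests on three assumptions: deaths are lost to the primary analysis, as the Sample Size section implies; the loss rates are 12% and 20%, as stated; and patients are treated as independent. The last is the protocol's own basis of calculation. Assignment by four-week periods is a separate matter that these figures leave out.

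The consequence is a moderate overstatement of power, not a flaw that invalidates the trial. It still needs correcting, because the target and the power claim cannot both be true.

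**What to change.** Rewrite the last sentence of the Sample Size section, and state there whether the 20% applies to all included patients or to those discharged alive. There are two ways to make it consistent:

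1. **Keep 252** and state that about 177 (sequential) or 171 (additive) patients are expected to be analysable, with 76% to 78% power for 60% versus 40% by the formula used for 188 (75% to 76% with pooled variance), before any allowance for assignment in four-week blocks.
2. **Keep 190 analysable** and state the total obtained by division: 190 / 0.704 = 270 (135 per arm) if losses are sequential, or 190 / 0.68 = 280 (140 per arm) if they are additive.

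The first option costs one sentence and a slightly less favourable power figure, with no extra recruitment. The second costs 18 to 28 additional patients and keeps the 80% claim under the stated assumptions.

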
disease severity (19). Therefore, preventing inactivity and loss of muscle strength during hospitalization is the best way to prevent DAH.

**Intervention Studies:** The first controlled clinical trials on the effectiveness of interdisciplinary geriatric acute care units designed to prevent or rehabilitate DAH have shown an improvement in functional status at hospital discharge (20, 21). Our interdisciplinary model in the acute care unit also demonstrates a benefit in reducing functional decline and the incidence of delirium during hospitalization (22). Various meta-analyses and systematic reviews demonstrate that interdisciplinary programs aimed at maintaining or improving the functional capacity of the elderly during hospitalization have the potential to improve functional status at discharge, as well as reduce mortality rates, length of stay, and institutionalization rates (23, 24). It seems that interventions that include a follow-up program can maintain positive effects for longer periods of time (24). These studies have limitations: they are very diverse in terms of the type of patients (young or very old elderly), lack a clear description of the type, frequency, and duration of rehabilitation program exercises. Additionally, due to being multidisciplinary programs focused not only on functionality, it is difficult to determine the isolated effect of exercise on functionality. A recent study explores the association of the different components of interdisciplinary models with functional improvement: medication review, early rehabilitation, and individualized treatment appear to be the most effective components (25). There are few studies on the effect of exercise separated from the other components of interdisciplinary models and show contradictory functional results (26, 27, 28).

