## STATISTICAL ANALYSIS

Groups will be compared using Student's t-test for continuous variables (or its nonparametric equivalent, the Mann-Whitney test), and chi-square test for categorical variables. The effect of training on outcome variables will be analyzed according to the principle of "intention-to-treat." The effect of training on the primary outcome variable, the proportion of patients who recover the Katz index at 3 months, will be analyzed using univariate and multivariate logistic regression. The effect of training on the recovery of other functional status scales will be analyzed similarly. The change in functional status from admission to discharge and 3 months will be classified as improvement if the number of independently performed ADLs increases or deterioration if the number decreases. Differences between groups will be analyzed using the chi-square test for linear trend. The effect of training on these functional scales as continuous variables will be analyzed using repeated measures analysis of variance (ANOVA) with two factors (between-subjects group and within-subjects time). The consistency of differences between the intervention and usual care in subgroups defined by age, frailty, presence of delirium, and baseline functional status will be analyzed using multivariate logistic regression with normal and ordinal models.

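### The sample size budgets in-hospital deaths as patients not analysed, although intention-to-treat is claimed and no rule says how a death counts in the primary outcome

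*Protocol*

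**What the plan says.** The Protocol's Primary Variable section sets the endpoint: "The proportion of patients who, at 3 months post-hospital discharge, recover the Katz index they had two weeks before admission (baseline) will be measured". It gives no rule for a patient who dies before that assessment.

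The Sample Size section takes its control rate from the group's earlier trial, where "in the control group, 40% of patients recovered their baseline Katz index at 3 months", and for the new programme "we expect that 60% will recover the Katz index at 3 months". With a power "of 80% and a significance level" "of 0.05 (two-tailed), we need to analyze a total of 188 patients", rounded to 190. It then adds two allowances, "Hospital mortality in our unit is approximately 12"% and a 20% loss to follow-up, and arrives at 252 to include, 126 per arm.

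The Statistical Analysis section says: "The effect of training on outcome variables will be analyzed according to the principle of" intention to treat. It excludes nobody and does not mention deaths. The Design section has mortality assessed at the 3-month telephone call, so vital status is meant to be known.

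**The concern.** Death is not missing data for this endpoint. Whether a patient regained the pre-illness Katz score by 3 months is settled once the patient has died: the answer is no. A sample size that places hospital deaths in the gap between included and analysed treats these known failures as absent observations. Intention-to-treat keeps them in the denominator of their assigned arm. The two sections therefore imply different primary analyses.

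Two things depend on which is meant. First, dropping deaths conditions on an event after randomisation, so the recovery proportion can shift with mortality while the number who recover stays the same. Second, the planning rates of 40% and 60% mean different things with and without deaths in the denominator, and so does the power at 252 patients. The Background reports three-month mortality of 10.7% against 36.7% between the groups with least and most functional deterioration. That is an association, not a treatment effect, but it shows that death and functional outcome are closely linked in such patients.

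**Working it through.** **1. Inputs (Sample Size section).** Rates 0.40 and 0.60; two-sided alpha 0.05; power 0.80; 188 rounded to 190 analysed; 12% hospital mortality; 20% loss; 252 included. The section does not say whether the 40% is a proportion of survivors or of all included patients.

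**2. The analysed number reproduces.** Unpooled normal approximation, per arm:

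n = (1.960 + 0.842)² × [0.40×0.60 + 0.60×0.40] / 0.20² = 7.849 × 0.48 / 0.04 = 94.19, or 188.4 in total, which matches 188.

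**3. The included number needs the 12%.**
- Both allowances: 190 × (1 + 0.12 + 0.20) = 250.8, which two equal whole-number arms bring to 252. The product 188 × 1.12 × 1.20 = 252.7 also fits.
- The 20% alone: 190 × 1.20 = 228, or 190 / 0.80 = 237.5, about 238.

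The loss allowance alone does not reach 252. The hospital deaths are handled as patients who do not reach the analysis.

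**4. How far the result could move if deaths were dropped.** Let the same proportion of all randomised patients recover in both arms, and let 40% be the control rate among survivors. With mortality mC (control) and mI (intervention), the survivor rate in the intervention arm is 0.40 × (1 - mC) / (1 - mI). Apart from the 12%, the mortality rates are assumptions:

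| mC | mI | Control, survivors | Intervention, survivors | Shift (points) |
|---|---|---|---|---|
| 12% | 8% | 40.0% | 38.3% | -1.7 |
| 12% | 16% | 40.0% | 41.9% | +1.9 |
| 25% | 20% | 40.0% | 37.5% | -2.5 |
| 25% | 30% | 40.0% | 42.9% | +2.9 |

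Each shift comes from the denominator alone. With equal mortality it is zero.

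**5. Power with deaths counted as non-recovery.** With 252 included and 20% lost, 252 × 0.80 = 201.6, about 202, are evaluable. Power is from the pooled normal approximation.
- *If 40%/60% are survivor rates*, with 12% mortality assumed in both arms: 0.88 × 0.40 = 35.2% and 0.88 × 0.60 = 52.8%, a difference of 17.6 points. Power is 71%. If every hospital death is observed and only survivors can be lost, 252 × 0.12 + 252 × 0.88 × 0.80 = 30.2 + 177.4 = 207.6, about 208 evaluable, and power is 73%.
- *If 40%/60% already count deaths as failures*: power at 202 evaluable is 82%, and the 12% allowance was not needed.

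**6. Size needed for 80% under the survivor reading.** The formula of step 2 gives 7.849 × (0.352×0.648 + 0.528×0.472) / 0.176² = 120.9 per arm, so 242 analysed (248 pooled). Dividing by 0.80 gives 303 (310) included.

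**The case against.** The strongest reply is that nothing in the analysis text removes deaths. The Statistical Analysis section claims intention-to-treat and the endpoint speaks of a proportion of patients; the 12% may be only a cautious recruitment allowance. Detailed handling of deaths may also sit in an analysis plan that is not shown. This stands to the extent that a reader might infer a declared survivors-only analysis, and the document declares none. What remains is a conflict within the Protocol itself: a sample size that sets deaths aside next to a principle that keeps them.

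Three further inferences are tempting and also not supported.
- That the comparison is among survivors at 3 months. Only in-hospital deaths are visibly budgeted out; later deaths are not mentioned, and whether the 20% loss includes them is unknown.
- That the sponsor expects the programme to change mortality. The Background does say that programmes have the potential to improve function "as well as reduce mortality rates, length of stay, and institutionalization rates", but it is describing reviews of interdisciplinary programmes. The hypothesis and objectives name no mortality effect. Differential mortality is an assumption of step 4.
- That 12% of enrolled patients will die in hospital. The figure is for the whole unit, and the Subjects section excludes terminal illness and recent myocardial infarction, among others, so mortality in the trial may be lower.

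It is also fair to say that the shifts in step 4 are small beside a planned difference of 20 points.

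**Conclusion.** The point holds as an inconsistency that needs correction. The step from 190 to 252 shows that in-hospital deaths are planned out of the primary denominator. That conflicts with the intention-to-treat statement and, with no rule for death in the endpoint, leaves the primary comparison open to two readings. The document does not establish that deaths will in fact be excluded, and it says nothing about deaths after discharge.

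The possible distortion is modest, about -2.5 to +2.9 points, and arises only if mortality differs between arms; the gaps used are assumed. The consequence for power is firmer: about 71-73% at 252 included if 40%/60% are survivor rates, against about 82% if deaths already count as failures. The lower figure rests on 12% mortality in both arms and no deaths after discharge. Further deaths would lower it.

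**What to change.** - Define the primary outcome for all randomised patients, in their assigned arm, as alive with a Katz index at or above the pre-illness value at 3 months. Count any death before that assessment, in hospital or after discharge, as non-recovery.
- Treat only true loss to follow-up as missing, for example by multiple imputation with a worst-case sensitivity analysis. Keep the survivors-only comparison as a secondary analysis.
- In the Sample Size section, remove the 12% from the attrition allowance and state whether the 40% and 60% are proportions of survivors or of all included patients. Put both rates on the new definition and restate the power at 252 included with 20% lost.

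No new data are needed, since mortality is already collected at the 3-month call. The cost is a revised definition, a revised calculation and possibly a less favourable stated power. If the planning rates prove to be survivor rates, the sponsor must either accept power of about 71-73% or include about 303 to 310 patients to restore 80%. Deleting the 12% and cutting recruitment without re-deriving the rates would make matters worse under that reading.
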